#### 2.5.2. Non-Tailored Group

The non-tailored group will complete the same questionnaire as the tailored group; participants in this group will be mailed a generic health promotion brochure promoting lifestyle changes. The generic material consists of an 8-page full-color booklet containing a generic set of information related to the illness and the lifestyle habits that should change after a diagnosis of hypertension or ACS.

#### 2.5.3. Usual Care Group

The usual care group will receive usual care from their physician, and they will complete the same assessment questionnaire as the other two groups. They will not be mailed any health promotion brochure.

### 2.6. Measurement of Outcomes

Patients will complete a self-report questionnaire six months post-randomization, and they will be asked to have a telephone interview twelve months post-randomization.

#### 2.6.1. Change in Lifestyle Habits

The primary outcome will be the change in behaviors, as measured six and 12 months after baseline. Changes in diet, physical exercise, alcohol intake, and smoking behavior will be evaluated singularly.

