## 2. Materials and Methods 

### 2.1. Design

The TTCYB study is a three-arm, parallel-group, randomized intervention designed to determine the effect of tailored print materials for patients with CVDs (see Figure 1). Follow-up assessments will occur at six and 12 months post-baseline evaluation.

At baseline and the six-month follow-up, patients will complete a series of self-report questionnaires evaluating lifestyle behavior, socio-demographic, and psychological characteristics. At the 12-month follow-up, patients will have a telephone interview that will assess lifestyle habits. After the baseline measurement, patients will be randomized into one of three groups: (1) the tailored group, which will receive tailored health brochures; (2) the “non-tailored” group, which will receive non-tailored health brochures; and (3) the usual care group, which will receive no print information materials. Participants will be assigned to one of the three study groups using a stratified randomization process characterized by the unpredictability of assignments. Patients in the tailored and non-tailored group will be mailed a health brochure after a baseline and a six-month evaluation. Within ten working days of completing the questionnaire, both at baseline and the six-month follow-up, the tailored (T) and non-tailored (NT) group will be mailed printed health materials while patients in the usual care (UC) group will receive no materials. Following the delivery of the materials, patients in the T and NT group will be contacted by phone for an interview to measure their judgment of the material. At the 12-month follow-up, all patients will have a telephone interview that will assess their lifestyle in terms of dietary behavior, physical activity, alcohol intake, and smoking behavior.

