#### 2.6.3. Patients’ Judgments about the Material

About seven days after the dispatch of the material, patients in the T and NT group will receive a telephone call in which they will be asked to judge the materials. The telephone survey will consist of dichotomous and five-point Likert scale questions. Table 3 explains the multiple questions in detail.

The same procedure (health material and telephone interview) will be conducted after the six-month follow-up.

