### 2.7. Sample Size Estimation

The power analysis was conducted in G*Power (G*Power, Brunsbüttel, Germany) on a repeated-measures ANOVA with within-between interaction with three measurements, three groups, with a correlation among repeated measures about 0.5, a power of 0.80, an alpha level of 0.05, and a small effect size (f = 0.10) [52]. The required sample size was found to be a minimum of 204 patients.

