## 3. Discussion

This report describes the rationale, design, and methods of the TTCYB study, a randomized controlled intervention that evaluates the efficacy of a tailored print intervention to improve healthy lifestyle in four behaviors (diet, physical activity, alcohol intake, and smoking behavior). This intervention targets a vulnerable and rapidly expanding segment of the population, CVD patients. The efficacy of the intervention in the tailored group compared to the non-tailored and usual care groups will be evaluated through patients’ judgments about the materials; changes in each one of the four lifestyle behaviors considered; improvements in body mass index, systolic and diastolic blood pressure; and medication adherence. If the TTCYB is efficacious, it will have implications for the design and implementation of tailored communication programs that aim at stimulating healthy behaviors to prevent worsening in patients with chronic diseases. The anticipated strengths of the study protocol include the target population, the longitudinal design, and the analysis not only of the intervention’s efficacy but also of the possible moderators of this efficacy. Besides, the intervention suggested in this protocol uses longitudinal tailoring based on models of health behavior combined in a way that has not been tested before to the best of our knowledge. The duration of the follow-up is one year, so it will be possible to investigate the long-term effects of the intervention. This project addresses major health issues and aims to contribute to the empirical and theoretical basis for developing effective primary and secondary preventive interventions. The proposed methodology can also be applied to other health problems that can benefit from lifestyle interventions. Finally, concepts from this study can potentially be extended to the primary prevention of cardiovascular diseases among high-risk groups.

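### Four separately judged primary behaviours at two visits, with no leading contrast, do not fit a sample size built on one three-arm test at 0.05

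*Protocol article*

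**What the plan says.** Section 2.6.1 of the protocol article defines the primary outcome: "The primary outcome will be the change in behaviors, as measured six and 12 months after baseline". It adds that "Changes in diet, physical exercise, alcohol intake, and smoking behavior will be evaluated singularly". Section 2.1 describes the design: "The TTCYB study is a three-arm, parallel-group, randomized intervention". The Discussion uses both comparators: "The efficacy of the intervention in the tailored group compared to the non-tailored and usual care groups will be evaluated through" several kinds of result, which include the four behaviours.

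The only significance level is in section 2.7, "an alpha level of 0.05". It belongs to a power calculation for one group-by-time interaction with three groups and three measurements, f = 0.10, correlation about 0.5 and power 0.80, giving a minimum of 204 patients. Section 2.9 plans repeated-measures ANOVA and, where appropriate, logistic and linear regression with baseline as covariate. It ranks no behaviour, visit or pair of arms.

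Section 2.6.3 says that "patients in the T and NT group will receive a telephone call in which they will be asked to judge the materials", and that this is repeated after the six-month mailing. One item of that survey (Table 3) asks whether the patient would change each of the four behaviours. The Discussion draws its implication for tailoring specifically: "If the TTCYB is efficacious, it will have implications for the design and implementation of tailored communication programs".

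**The concern.** There are two separate difficulties.

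**Error rate.** The sample size assumes one test at 5%. The primary outcome as defined leads to at least four. Because the article does not say what result would establish efficacy, a reader of the final report cannot tell whether one positive behaviour out of four was the planned criterion or was picked afterwards.

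**Question answered.** A three-arm interaction test rejects when any arm departs from the others. If both brochures work equally well and usual care does not change, the test can be significant although tailoring adds nothing. Usual care also differs from the brochure arms by more than the brochure. Only the brochure arms are telephoned, and those calls raise the very behaviours that form the primary outcome. The one comparison with equal mailing and equal contact is tailored versus non-tailored, and nothing gives it priority.

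**Working it through.** **1. The plan's own figure.** Inputs from section 2.7: k = 3 groups, m = 3 measurements, ρ = 0.5, f = 0.10, α = 0.05. Sphericity is assumed.

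- λ = f²·N·m/(1 − ρ) = 0.01 × 204 × 3/0.5 = 12.24
- df1 = (k − 1)(m − 1) = 4; df2 = (N − k)(m − 1) = 201 × 2 = 402
- Critical F = 2.394; noncentral F power = 0.806

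The smallest N that reaches 0.80 is 202. The smallest multiple of three is 204 (68 per arm). The stated size reproduces, for one such test.

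**2. What that test can detect.** λ depends on f only, not on which arm differs. The power of 0.806 therefore applies equally to a pattern in which tailored and non-tailored are identical and only usual care differs. A significant result does not distinguish the two.

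**3. Chance of at least one false positive.** All nulls are true, each test is at 0.05, and any one positive counts. Between-behaviour correlation is assumed at 0 to 0.5. The correlation between the two visits is taken as 0.5, or as 1/3 after baseline adjustment: (0.5 − 0.25)/(1 − 0.25).

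| Family of tests | Risk |
|---|---|
| One test per behaviour, independent: 1 − 0.95⁴ | 18.5% |
| One test per behaviour, correlation 0.5 (simulated) | about 15-16% |
| Four behaviours × two visits, one contrast (simulated) | about 27-33% |
| Four behaviours × two visits, tailored vs each control (simulated) | about 44-52% |

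Only the first two rows follow from the analysis as described. The last two need separate tests that the article permits but does not state.

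**4. Power after correction.** Holm compares the smallest of four p-values with 0.05/4 = 0.0125.

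- Omnibus test, N = 204, α = 0.0125: critical F = 3.234, power = 0.629. Reaching 0.80 would need N = 272 (273 with equal arms).
- Tailored vs non-tailored at one visit, 68 per arm, baseline-adjusted with correlation 0.5, no dropout: noncentrality = d/√(1 − 0.5²) × √(68/2) = 6.733·d. The critical z is 2.498, and power ≈ Φ(6.733·d − 2.498).

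| Assumed standardised difference d | Noncentrality | Power |
|---|---|---|
| 0.2 | 1.347 | 0.12 |
| 0.3 | 2.020 | 0.32 |
| 0.4 | 2.693 | 0.58 |
| 0.5 | 3.367 | 0.81 |

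The article gives no pairwise effect size, so d is an assumption and the range is shown.

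**The case against.** The strongest reply is that the article never says each visit and each pair of arms is tested at 0.05. Alpha appears only in the sample-size section, and one repeated-measures ANOVA per behaviour can cover both follow-ups and all three arms. A multiplicity procedure may also sit in an analysis plan that is not shown, so its absence here is not a fault. All of this stands. A reader might infer from the number of behaviours, visits and comparators that efficacy could be declared with a false-positive risk near 50%. The document does not support that reading, because it states neither the separate tests nor a rule that any one of them suffices.

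It can also be said that evaluating the behaviours singly points to four behaviour-specific conclusions, each with its own 5% error. That is a coherent position, but the article does not adopt it: it speaks of whether the intervention as a whole is efficacious.

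On the calls, usual care without materials is the declared comparator, and the calls are described as measuring judgments of the material. This is fair. Table 3 makes an influence on behaviour plausible, but nothing in the article indicates its size, and tailored versus non-tailored is unaffected.

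What remains does not depend on an unseen plan. The article itself fixes a four-part primary outcome at two visits, a sample size for one test, and a test that does not isolate tailoring.

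**Conclusion.** The point holds in this limited form. Section 2.6.1 sets four separately judged primary behaviours at two visits without a leading behaviour, visit or contrast, while section 2.7 supports one omnibus test at 0.05. If significance on any one behaviour were read as efficacy, the risk is about 15-19%, roughly three to four times the nominal level. This rests on two assumptions: that success rule, and between-behaviour correlations of 0.5 to 0. The higher figures apply only if visits and control comparisons were tested separately.

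Independently of alpha, the powered test does not answer whether tailoring works, and comparisons with usual care combine the brochure with the telephone calls.

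**What to change.** In sections 2.6.1 and 2.9, state that tailored versus non-tailored is the confirmatory contrast for each behaviour at one named visit (12 months, for example), with Holm across the four behaviours at overall 0.05. Make the other visit and all usual-care comparisons secondary, and describe the latter as brochure plus calls versus usual care.

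In section 2.7, add a power statement for the pairwise contrast at 68 per arm. The omnibus figure (0.81, or 0.63 at 0.0125) does not apply to it. Under the assumptions above, power at the first Holm step is about 0.58 for a difference of 0.4 and 0.81 for 0.5, before any dropout. Restate the power openly rather than enrol more patients.

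This changes analysis text only and no procedure for patients. The cost is lower power per behaviour, which is severe if the true difference is small (about 0.12 at 0.2). Naming one primary behaviour and keeping the powered interaction test would leave N = 204 and alpha 0.05 unchanged, but would not by itself isolate tailoring.

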#### 2.6.2. Physiological Parameters

The secondary outcomes to be measured will be changes in physiological parameters related to (a) body mass index (BMI), (b) waist circumference; (c) blood pressure values, (d) the existence of diabetes mellitus, and (e) medical adherence between the baseline and the six-month follow-up.

#### 2.6.3. Patients’ Judgments about the Material

About seven days after the dispatch of the material, patients in the T and NT group will receive a telephone call in which they will be asked to judge the materials. The telephone survey will consist of dichotomous and five-point Likert scale questions. Table 3 explains the multiple questions in detail.

The same procedure (health material and telephone interview) will be conducted after the six-month follow-up.

#### 2.6.4. Potential Moderators of Intervention Efficacy

Even though there is strong evidence on the greater efficacy of tailored print materials in changing health behavior [13,14,15,16,17,18,19], there is still a lack of evidence on the moderator variables for which tailored materials work in certain conditions and for a certain population. Previous studies have called for new research to identify the reasons tailoring works in some groups and not in others [19,47] but stopped short of suggesting which variables to study. The TTCYB intervention also has the aim to understand if psychological variables related to locus of control, self-efficacy, anxiety, depression, and illness perception could moderate the efficacy of the tailored print material.

#### 2.6.5. Locus of Control

Patients’ beliefs about their disease are assessed with the Multidimensional Health Locus of Control Scale (MHLC), Form C [48], which makes it possible to detect if a patient considers health-related outcomes as a result of his/her actions, luck or chance, or the influence of others such as health professionals or family members. It is an 18-item self-report measure on a six-point scale ranging from 1 (strongly disagree) to 6 (strongly agree). It has been used in studies to make predictions about health behavior [49] and has shown good reliability and validity in a variety of chronic illness populations [48].

#### 2.6.6. Anxiety and Depression

Anxiety and depression are evaluated through the Hospital Anxiety and Depression Scale (HADS), a self-administered questionnaire specifically developed to detect states of anxiety and depression in the setting of hospital out-patient clinics [50]. It is composed of two seven-item scales (one for anxiety and one for depression), which should be used as two separate measures of emotional disturbance. All items are scored on a four-point scale from 0 to 3.

#### 2.6.7. General Self Efficacy

General self-efficacy (not specifically related to behavioral change) is assessed with the General Self-Efficacy Scale, a 10-item scale designed to assess optimistic self-beliefs to cope with a variety of difficult demands in life [51]. Possible responses are not at all true (1), hardly true (2), moderately true (3), and exactly true (4), yielding a total score between 10 and 40.

### 2.7. Sample Size Estimation

The power analysis was conducted in G*Power (G*Power, Brunsbüttel, Germany) on a repeated-measures ANOVA with within-between interaction with three measurements, three groups, with a correlation among repeated measures about 0.5, a power of 0.80, an alpha level of 0.05, and a small effect size (f = 0.10) [52]. The required sample size was found to be a minimum of 204 patients.

### 2.8. Data Collection Methods and Data Management

Each center’s personnel will be trained centrally in the study requirements, standardized measurement and the eliciting of information from study participants in a uniform reproducible manner. All data will be entered electronically at the Coordinating Center (University of Milan Bicocca). Original study forms will be entered and kept on file at the Coordinating Center. All forms, files, and datasets related to study data will be kept in locked cabinets. Access to the study data will be restricted. A password system will be utilized to control access; these passwords will be changed regularly. All reports prepared by study group members will be prepared such that no individual subject can be identified.

### 2.9. Planned Statistical Analysis

Demographic data (e.g., age, gender) will be described for the total group and the subgroups separately. Continuous variables will be denoted with means, standard deviations, and medians. Categorical variables will be denoted in numbers and percentages. Group differences in behavior and physiological (BMI and blood pressure value) changes will be tested with a repeated-measures ANOVA and logistic and linear regression as appropriate, using the baseline values of these endpoints as covariates. Regressions will also be used to test for interactions of type of material with factors such as self, efficacy, locus of control, age, gender. This strategy will allow us to test whether the intervention works better in specific groups over others. Concerning patients’ judgments of the material, a *t*-test analysis and a Cross-table with chi-square statistic will be performed. All analyses will be conducted using the Statistical Package for the Social Sciences (SPSS) version 24.0 for Windows (SPSS Inc., Chicago, IL, USA) and MPlus software Version 7.0 (Muthén & Muthén, Los Angeles, CA, USA).

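### The trial is sized on a three-group interaction and fixes no tailored versus non-tailored contrast for the behaviours, so a significant result would not by itself show that tailoring works

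*Protocol article*

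**What the plan says.** Section 2.1 describes a three-arm randomised study "designed to determine the effect of tailored print materials for patients with CVDs". The arms are a tailored brochure (T), a generic brochure (NT) and usual care with no brochure (UC). Section 3 frames efficacy as T compared with both NT and UC, and adds: "If the TTCYB is efficacious, it will have implications for the design and implementation of tailored communication programs".

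Section 2.7 bases the sample size on a "repeated-measures ANOVA with within-between interaction with three measurements, three groups". Its other inputs are f = 0.10, alpha 0.05, 80% power and a correlation of 0.5 between a patient's measurements. The result is a minimum of 204 patients.

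Section 2.9 says: "Group differences in behavior and physiological (BMI and blood pressure value) changes will be tested with a repeated-measures ANOVA". The same sentence adds logistic and linear regression where suitable, with the baseline value of the endpoint as a covariate. Type of material is mentioned for regressions that test moderator interactions. Patients' judgments of the brochures get a t-test and a chi-square test. These judgments are collected only in the T and NT groups, so this is a direct comparison of the two brochures. No such comparison is fixed for diet, physical activity, alcohol or smoking.

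**The concern.** The NT arm is what separates the effect of tailoring from the effect of receiving any brochure. A three-group interaction does not make that separation. Its null hypothesis is that all three arms have the same time profile, which is false as soon as brochures of any kind differ from no brochure, even when T and NT are identical.

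The intended conclusion is about tailored communication programmes. Under the plan as written, a significant result on a behaviour could be reported in support of tailoring when it shows only that mailing a brochure differs from mailing none. The problem exists for a single behaviour tested once at 0.05, so it is separate from multiplicity. The stated power of 0.80 likewise refers to the three-group interaction and does not tell the reader how well the trial can compare T with NT.

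**Working it through.** **Inputs.** From section 2.7: k = 3 groups, m = 3 measurements, correlation ρ = 0.5, alpha 0.05, f = 0.10, N = 204. Assumed, because the article does not give them: equal allocation (n = 204/3 = 68 per arm), sphericity and no dropout. Effects are in SD units and are present equally at 6 and 12 months (a step pattern).

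**1. Reproducing N = 204.** For the interaction, λ = f²·N·m/(1 − ρ) = 0.01 × 204 × 3 / 0.5 = 12.24, with df = (3 − 1)(3 − 1) = 4 and (204 − 3)(3 − 1) = 402. The noncentral F gives power 0.806. N = 201 gives 0.799, so 204 is the smallest N divisible by three that reaches 0.80. The powered test is therefore the 4-df omnibus interaction.

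**2. What f = 0.10 means if T = NT.** With a step of d SD in both brochure arms and none in UC, the interaction effect is f = 2d/9. Hence f = 0.10 corresponds to d = 0.45. The same f arises if T alone differs by 0.45 SD. The effect size is not tied to any pair of arms.

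**3. Rejection rates when T = NT and both differ from UC by d.** Here λ = (2d/9)² × 204 × 3 / 0.5.

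| d (SD) | f | λ | Three-group interaction rejects | T versus NT test rejects |
|---|---|---|---|---|
| 0 | 0 | 0 | 5% | 5% |
| 0.20 | 0.044 | 2.42 | 20% | 5% |
| 0.30 | 0.067 | 5.44 | 42% | 5% |
| 0.45 | 0.100 | 12.24 | 81% | 5% |

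Simulation of 20,000 trials at d = 0.45 gave 0.806 for the interaction and 0.047 for the T versus NT interaction. A linear rather than step pattern at f = 0.10 gave 0.805 and 0.053.

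Section 2.9 also mentions baseline as a covariate. For a three-group test on the mean of the two follow-ups, the residual variance is (1 + 0.5)/2 − 0.5² = 0.50. The test rejects 37.6%, 72.0% and 97.5% of the time at 0.20, 0.30 and 0.45 SD. Adjustment makes the three-group test more sensitive to a brochure effect but no more specific to tailoring.

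**4. Power of T versus NT at N = 204.**

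- T versus NT interaction: λ = n·δ²/[3(1 − ρ)] with 2 and 268 df, where δ is the T − NT difference.
- Baseline-adjusted contrast on mean follow-up, from the three-arm model: λ = δ²/(2 × 0.50/68) with 1 and 200 df.

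| Scenario, each at three-group f = 0.10 | δ | T versus NT interaction | Adjusted T versus NT contrast |
|---|---|---|---|
| Only tailoring works (T 0.45, NT = UC) | 0.45 | λ = 9.18, 77% | λ = 13.77, 96% |
| NT has half the T effect (T 0.52, NT 0.26, UC 0) | 0.26 | λ = 3.06, 32% | λ = 4.59, 57% |

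The three-group interaction has power 0.806 in both scenarios, so the 0.80 in section 2.7 does not carry over to the comparison of the two brochures.

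**The case against.** Several points on the other side are sound.

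- **The rejection is correct.** When both brochures differ from UC, the omnibus null is false and rejecting it is not a type I error. The article does not say that a significant interaction will count as proof of tailoring. This stands: the point concerns what the result can support.
- **The omnibus test is not the only one named.** The regressions could yield arm-by-arm coefficients. True, but they are listed without any contrast being fixed.
- **UC is a declared comparator.** Efficacy is framed against both control groups, so T versus UC belongs to the question. This stands, and the fix keeps it.
- **This is a condensed article, and follow-up contrasts are often left to an analysis plan.** Fair, and the missing detail alone would be no finding. However, what N = 204 and the 0.80 refer to is fully stated here, and it does not match the comparison behind the tailoring claim.

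Two stronger readings are tempting. A reader might infer that the test rejects about 80% of the time whenever tailoring adds nothing. It does so only if both brochures differ from UC by the full design effect; the rate is 5% if all arms are alike. A reader might also infer that the omnibus test is less powerful than a direct contrast when tailoring does work. Setting an unadjusted interaction (81%) beside an adjusted contrast (96%) suggests this, but that gap comes from baseline adjustment and averaging, and section 2.9 already plans baseline adjustment. Like for like, if only tailoring works at 0.45 SD, the three-group test is slightly more powerful: 80.6% against 77.4% unadjusted, and 97.5% against 95.8% adjusted.

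**Conclusion.** The concern holds in a limited form. The test that is sized, and named first for behaviour change, does not address the T versus NT comparison, and no contrast that does is fixed for the primary behaviours. With T = NT, a significant three-group interaction occurs in 5% to 81% of trials as the shared brochure effect rises from zero to 0.45 SD. That would be an error only if reported as evidence for tailoring. The documents support neither an unconditional rate near 80% nor a loss of power from the omnibus test.

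The figures rest on equal allocation, correlation 0.5, sphericity and complete data. With sphericity epsilon 0.95, the 81% becomes 79%. With 10% loss it becomes about 76%, and with 20% loss about 69%. This is a cheap improvement worth making before analysis.

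**What to change.** **Section 2.9.** For each behaviour, rest the claim about tailoring on the baseline-adjusted T versus NT contrast from the model fitted to all three arms. Report T versus UC and NT versus UC as separate contrasts, since usual care is also a declared comparator. State that a significant three-group interaction is not by itself evidence for tailoring.

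**Section 2.7.** Say that the 0.80 refers to the three-group interaction, and give the T versus NT power at N = 204 beside it with its assumptions. If only tailoring works at 0.45 SD, this is about 77% for the T versus NT interaction or 96% for the adjusted contrast. If the generic brochure has half the tailored effect at the same f, it is about 32% or 57%.

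**Cost.** Wording only, with no new data or patients. A result driven only by brochure versus no brochure could no longer be reported as success for tailoring, and the stated T versus NT power may look less favourable than 0.80.

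### The repeated-measures ANOVA named for the four behaviours, if run in its classical complete-case form, discards observed 6-month data, loses power and can bias the arm differences when dropout differs by arm

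*Protocol article*

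**What the plan says.** Section 2.6.1 of the protocol article sets the endpoint: "The primary outcome will be the change in behaviors, as measured six and 12 months after baseline", with each of the four behaviours evaluated separately. Section 2.9 states that group differences in behaviour and physiological change "will be tested with a repeated-measures ANOVA and logistic and linear regression as appropriate, using the baseline values of these endpoints as covariates". The software is SPSS 24 and Mplus 7.

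Section 2.7 sizes the trial on a "repeated-measures ANOVA with within-between interaction with three measurements, three groups". Its other inputs are a common correlation of 0.5 between waves, 80% power, a 5% significance level and an f of 0.10. It concludes: "The required sample size was found to be a minimum of 204 patients". No dropout rate or inflation appears.

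The 12-month wave is collected differently from the others. Section 2.6 has patients complete a questionnaire at 6 months, and then "they will be asked to have a telephone interview twelve months post-randomization". Table 1 shows the behaviours measured at all three times and the clinical evaluation at baseline and 6 months only.

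**The concern.** A classical repeated-measures ANOVA needs a complete row for each patient. A patient who answers at 6 months and cannot be reached by telephone at 12 months drops out of the whole analysis, including the 6-month comparison for which the data exist.

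Two things follow. Power is lost. In addition, the 6-month comparison is restricted by an event that happens after it. If that event depends on the 6-month score, and does so differently by arm, the completers are no longer comparable.

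The design makes this possible, although nothing shows that it will happen. After the 6-month questionnaire the tailored arm is mailed personal feedback based on its own answers, the non-tailored arm a generic brochure, and usual care nothing (sections 2.1 and 2.5). If poorly performing tailored patients leave more often, the tailored completers look better than the arm really is. The primary outcome is what would be affected.

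**Working it through.** **Step 1. Reproduce the stated sample size.** Inputs from section 2.7: f = 0.10, m = 3 measurements, k = 3 groups, ρ = 0.5, alpha 0.05. Sphericity is assumed (ε = 1).

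- Noncentrality: λ = f²·N·m/(1 − ρ)
- df1 = (k − 1)(m − 1) = 4; df2 = (N − k)(m − 1)
- N = 204: λ = 0.01 × 204 × 3 / 0.5 = 12.24, df2 = 402, power 0.806

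The smallest N reaching 0.80 is 202, or 204 as a multiple of three. The stated figure reproduces, for complete data.

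**Step 2. Power if only completers are analysed.** The loss rates are assumptions.

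| Loss | Completers from 204 | λ | Power | Recruits needed for 204 completers |
|---|---|---|---|---|
| 10% | 184 | 11.04 | 0.76 | 204/0.9 → 227 |
| 20% | 163 | 9.78 | 0.70 | 204/0.8 = 255 |
| 30% | 143 | 8.58 | 0.63 | 204/0.7 → 292 |

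**Step 3. Bias of the completer analysis.** I compared two arms by simulation with very large arms (600,000 or more patients each) and outcome SD 1. All 6-month values are observed, and loss at 12 months follows a logistic function of the 6-month score. The estimate is the arm difference adjusted for baseline, in completers. Columns 3 and 4 differ in the assumed correlations (0–6, 6–12 and 0–12 months).

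| Dropout assumption | Bias at 6 months (SD) | 12 months, 0.5/0.5/0.5 | 12 months, 0.5/0.5/0.25 |
|---|---|---|---|
| Random, 20% per arm | 0.00 | 0.00 | 0.00 |
| Same rule in both arms, no effect | 0.00 | 0.00 | 0.00 |
| Same rule, true effect 0.25 | −0.02 | about −0.01 | about −0.01 |
| Same slope (0.5), 10% v 30% loss | 0.07 | 0.02 | 0.035 |
| Slope 1 in one arm, 0 in the other, 20% each | 0.13 | 0.04 | 0.07 |
| Opposite slopes of 0.5, 20% each | about 0.15 | 0.05 | 0.07 |

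An analysis of all observed values gives 0.00 at both times in every row.

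**Step 4. Why 12 months is affected less.** Given baseline, the 12-month score depends on the 6-month score with slope b = (r₆,₁₂ − r₀,₆·r₀,₁₂)/(1 − r₀,₆²). The 12-month bias is b times the 6-month bias.

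- Correlations all 0.5: b = (0.5 − 0.25)/0.75 = 1/3, so 0.13 × 1/3 = 0.04
- 0.5/0.5/0.25: b = (0.5 − 0.125)/0.75 = 0.5, so 0.13 × 0.5 = 0.07
- 0.5/0.6/0.35: b = (0.6 − 0.175)/0.75 = 0.57, so 0.13 × 0.57 = 0.07

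With 30% loss and a slope of 1 in one arm only, the 6-month bias is 0.19 to 0.20. The 12-month bias then runs from 0.195 × 1/3 = 0.07 to 0.195 × 0.57 = 0.11. Over 20% to 30% loss the ranges are 0.13 to 0.20 SD at 6 months and 0.04 to 0.11 SD at 12 months. If the comparator's slope is half as steep rather than zero, the biases are a little under half of these.

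**Step 5. Effect on the test itself.** With 68 per arm, no true effect, 20% to 30% loss and a slope of 1 in at least one arm, the completer three-group interaction test has a type I error of about 0.06 to 0.09. A pairwise completer comparison at 6 months, adjusted for baseline, has 0.12 to 0.19.

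**The case against.** **The text does not say that patients with a missed visit are excluded.** This is correct. Complete-case use is a property of the classical procedure. The same sentence also allows regression: a 6-month score regressed on arm and baseline uses everyone seen at 6 months, and the 6-month bias then disappears. That part of the objection stands. It does not rescue 12 months, because a regression on baseline alone still drops those missing at 12 months and ignores their 6-month score.

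**The bias is conditional.** A reader might infer that the ANOVA will bias the result. The article does not support that. It gives no dropout rate or mechanism, and several plausible mechanisms give a bias of zero or about 0.02 SD or less.

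**The larger error rate belongs to another test.** A reader might carry the 0.12 to 0.19 over to the planned analysis. It applies to a pairwise completer contrast. For the interaction test in section 2.7 the inflation is modest.

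**Missing-data handling may sit in the full protocol or analysis plan.** Its absence from an article is not an error, and none is claimed. The point concerns the method that the article does name.

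**The alternative looks perfect only by construction.** This is also fair. Dropout was simulated to depend on an observed score. If it depends on unobserved values, or patients leave before 6 months for unrecorded reasons, a likelihood analysis can be biased too.

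**Conclusion.** The point holds in a limited form. Run classically, the named repeated-measures ANOVA wastes 6-month data. The power loss needs only that some patients miss a wave: from 0.80 to about 0.76, 0.70 or 0.63 at 10%, 20% or 30% loss. Bias is a possibility rather than a prediction. It reaches about 0.13 to 0.20 SD at 6 months and 0.04 to 0.11 SD at 12 months only if 20% to 30% leave and leaving is strongly tied to the 6-month score in one arm and not in the other.

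The mechanism concerns the four behaviours alone. A reader might extend it to BMI and blood pressure, but these have a single follow-up, so a missed 12-month interview cannot remove their 6-month value. The point is worth acting on because a better method is available at little cost in software already listed.

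**What to change.** In section 2.9, for the behaviour scores analysed as continuous, replace the repeated-measures ANOVA with a linear mixed model, or with full-information maximum likelihood in Mplus. Use the 6- and 12-month scores as outcomes; arm, time, arm-by-time and baseline score as terms; and an unstructured covariance. Include every randomised patient with at least one follow-up, and report the adjusted arm differences at 6 and at 12 months.

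The cost is a change of wording and slightly more analysis work. The model relies on data being missing at random given baseline, arm and the observed follow-up, which is a weaker assumption than the completer analysis needs. It does not recover patients with no follow-up at all.
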